### Randomisation

After enrolment, infants will be randomly allocated to the intervention (CareToy training) or control group using a computer generated set of random pair 1:1 allocation (CareToy training – standard care or standard care – CareToy training). These random sets will be sealed in numbered envelopes.

### Blinding

Caregivers, therapists and study personnel who follow the infants during the trial will not be blinded about the allocation group. Outcome measures (Infant Motor Profile, IMP; Alberta Infant Motor Scale, AIMS; Bayley Scales of Infant Development III Edition, BSID-III) will be performed, videotaped and scored by assessors who are blinded to group allocation.

### Therapy protocols

#### CareToy training

On the base of each infant’s developmental needs, the rehabilitation staff (e.g. child neurologists and paediatric physical therapists) will plan a series of individualized goal-directed activities (rehabilitation packages) mainly focused on postural control, reaching, grasping, manipulation, visual attention and orientation in supine, prone and/or sitting position. According to the planned activities, the CareToy system will be personalized and delivered at the home of the infant. The CareToy training will be used daily for 4 weeks (28 days). Each daily training lasts about 30-45 minutes and consists of various activities of 2-10 minutes duration performed during the day when the infant is in active state and compliant.

Daily training will be remotely monitored by the rehabilitation staff, who may modify the rehabilitation packages according to infant’s developmental needs and progress. Caregivers will fill out a questionnaire at the end of each training session to record acceptance and compliance to the activities by the infant. The drop-out criterion for each daily session is if the infant completes less than 51% of the planned scenarios.

Caregivers will be trained in playing with their infant through the CareToy system during the first training week by the rehabilitation staff. In the following 3 weeks of training, support and advice will be given, even on site if necessary.

#### Standard care

Standard care refers to the current care advice, which is similar in Pisa and Copenhagen, in the management of preterm infants in the first months of life.

### Outcome measures

During the study period infants will be assessed at baseline and then at three different time points (Figure 2).

The infants' assessment will be performed in each clinical centre, by blinded assessors, who are trained in the use of the outcome scales. To guarantee a high level of evaluation and score agreement, during the months preceding the beginning of the study, the assessors had worked together sharing assessments and scores.

The assessment of motor development has been chosen as primary outcome measure using IMP. The following secondary outcomes have been chosen: AIMS, BSID-III Cognitive subscale and Teller Acuity Cards®. Each assessment can be done in two consecutive days to ensure greater compliance by the infant.

### Primary outcome measure

#### Infant Motor Profile (IMP)

It is a new, video-based and qualitative assessment of motor behaviour in infancy, applicable in preterm and at term infants aged 3 to 18 months [33]. It consists of 80 items addressed to explore the child's motor abilities and to evaluate motor behaviour in five domains: i) variation, ii) variability (ability to select motor strategies), iii) movement fluency, iv) movement symmetry and v) motor performance.

IMP consists of spontaneously and elicited motor behaviour recording while the infants are in supine, prone, sitting, standing, walking (depending on infants' age and functional capacity), reaching, grasping, and manipulation of objects in supine and in supported sitting positions. The assessment lasts approximately 15 minutes. The total IMP score is constituted by the mean of the five domain scores. It is scored off-line on the basis of the video recordings.

This tool is intended to detect and quantify changes after intervention and it is reported as having a satisfactory intra and inter-observer reliability and a good score reliability. In particular, it has been demonstrated that the inter-observer reliability of the total IMP score yielded an ICC of 0.94 (95% CI 0.87–0.97), and the reliability of scoring the IMP domains moderate to good, with ICCs ranging from 0.69 to 0.99. Moreover a strong correlation between IMP performance domain score and AIMS has been found [33, 34]. This evaluation will be carried out at all four time-points (T0-T3), but only the change from T0 to T1 will be used as the primary outcome.

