### Study sample and recruitment

The study population will consist of preterm infants recruited at the local Neonatology Units (“Santa Chiara” University Hospital in Pisa and Rigshospitalet in Copenhagen). Eligible infants will be identified according to strict inclusion and exclusion criteria (see below) by the Neonatology teams before the discharge. They will inform the caregivers about the study and, if interested, the information letter and the informative flyer about the project will be given. Recruitment should take place after discharge until 9 months of corrected age. If the parents accept to participate they will provide their written informed consent for the infant to take part of the study. Extensive perinatal data will be collected from medical records and the infants will be evaluated on the basis of a standard neurological examination (Hammersmith Neurological Examination, HINE [28, 29] and by Prechtl’s General Movements Assessment, GMA [30, 31]).

The clinical trial has been approved by the Ethics Committee of Pisa University Hospital (Italy), Tuscan Region Pediatric Ethics Committee (Italy) and to Ethics Committee of Region Hovedstaden (Denmark). Moreover, the Italian Ministry of Health has approved the trial considering that the CareToy is configured as a medical device without a CE mark.

This study will include preterm infants that met the following criteria:

Inclusion Criteria:

 gestational age ≥28 + 0 weeks and 32 + 6 weeks corrected age at baseline: between 3 and 9 months; achievement of predefined cut off scores in gross motor ability derived from Ages & Stages Questionnaire® Third Edition (ASQ-3), in relation to corrected age [32].

In detail:4 months form (from 3 months to 4 months 30 days) score ≥10;6 months form (from 5 months to 6 months 30 days) score ≥5 - <50;8 months form (from 7 months to 8 months 30 days) ≥10 - <30

Exclusion Criteria:

 infants with gestational age <28 weeks or ≥33 weeks infants small for gestational age (i.e. weight below the 10^th^) presence of brain damage i.e. brain malformation, intra-ventricular haemorrhage (IVH) >1; any degree of periventricular leukomalacia (PVL) known epilepsy or other form of seizure severe sensory deficits (blindness, deafness) other severe non neurological malformations participation in other experimental studies having rehabilitation aims

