### Sample size

According to CONSORT guidelines [26, 27] the sample size estimates were based on projected treatment effect on the primary outcome measure, the Infant Motor Profile (IMP [33, 34], see below). A sample of 36 infants is required to detect a clinically relevant change of 7.5 points in the total IMP score (SD = 8.2) at significance level of 0.05 and 80% power [35]. Considering a 10% of possible drop-outs a minimum of 40 infants will be recruited. Twins will always be assigned to the same group, in order to facilitate the parents in managing the CareToy system for their infants.

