### Analyses

Clinical Data will be managed and analysed using the Statistical Package for Social Sciences (SPSS). Descriptive statistics (means, standard deviation) will be calculated to summarise the data set for both groups and to identify potential baseline differences between the groups; p values will be used to indicate the strength of the evidence, and the Bonferroni correction for multiple assessments will be performed. The primary level of analysis will be the assessment of the effects of CareToy training at the primary endpoint (T1) in the primary and then in the secondary outcome measures. In the second level analysis we will provide multivariate statistics in order to take into account effect modifiers such as basal level of motor development, family compliance and time of training.

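### The primary IMP comparison uses change from T0 and leaves baseline motor level to a second-level analysis, giving up precision that adjustment for T0 IMP would recover

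*Protocol article*

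**What the plan says.** In the protocol article, the section Infant Motor Profile (IMP) says the scale is scored at T0, T1, T2 and T3, but that "only the change from T0 to T1 will be used as the primary outcome".

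The Analyses section sets two levels. The primary level is the effect of training at T1, on the primary and then the secondary outcomes; no covariate is named there. Descriptive statistics are to be used "to identify potential baseline differences between the groups", with no statement of what follows if differences are found. Baseline motor level appears only at the second level, which is to deal with "effect modifiers such as basal level of motor development, family compliance and time of training".

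The Sample size section asks for 36 evaluable infants for a 7.5-point difference with an SD of 8.2, at significance level 0.05 and 80% power, and raises this to 40 for 10% drop-out. It does not say whether 8.2 is the SD of the change or of the score at one visit.

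**The concern.** A change score subtracts the whole T0 value, which is the best use of T0 only when T1 moves one-for-one with it. If the slope of T1 on T0 is r < 1, an arm that starts lower by chance tends to gain more whatever the treatment, and a fraction (1 - r) of the T0 difference stays in the estimate. ANCOVA on T0 removes that part and has a smaller residual variance.

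The article has T0 IMP on every infant but assigns baseline level to a later analysis that also includes family compliance and time of training. On their natural reading these are known only after allocation. A model that conditions on them does not estimate the randomised effect, so the second level cannot stand in for a baseline-adjusted primary result.

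With about 18 evaluable infants per arm, the difference in precision could be worth several points of power at no cost in recruitment.

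**Working it through.** **Inputs.** From Sample size: difference 7.5, SD 8.2, alpha 0.05 (two-sided assumed), 36 evaluable, so 18 per arm. Not in the article: the T0-T1 correlation r, shown here from 0.3 to 0.9. Assumed: equal variance σ² at T0 and T1, infants treated as independent, and, for the main table, 8.2 as the SD of change.

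**1. The plan's own figure.** Normal approximation: total N = 4 × (8.2 × (1.960 + 0.842) / 7.5)² = 37.5, or 38 after rounding up per arm, within two infants of the stated 36. Then 36 / 0.9 = 40, as stated.

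**2. Power of the unadjusted change score.** The standard error is 8.2 × √(2/18) = 2.73. The noncentrality is 7.5 / 2.73 = 2.74 on 34 df, which gives 76.0% power.

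**3. Variance ratio.** Var(change) = 2σ²(1 - r) and Var(ANCOVA) = σ²(1 - r²), so the ratio is (1 + r)/2. The ANCOVA residual SD is 8.2 × √((1 + r)/2).

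**4. Charging for the covariate.** With N = 36 and q covariates, chance covariate imbalance inflates the variance of the arm effect by an expected (N - 3)/(N - q - 3). For q = 1 this is 33/32 = 1.031, with 33 df. Example at r = 0.5: 7.5 / (7.10 × √(2/18 × 1.031)) = 3.12, giving 85.7%.

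| r | (1 + r)/2 | ANCOVA SD | Power, change score | Power, ANCOVA on T0 IMP |
|---|---|---|---|---|
| 0.3 | 0.65 | 6.61 | 76.0% | 90.2% |
| 0.5 | 0.75 | 7.10 | 76.0% | 85.7% |
| 0.7 | 0.85 | 7.56 | 76.0% | 81.1% |
| 0.9 | 0.95 | 7.99 | 76.0% | 76.7% |

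**5. If 8.2 is the SD at one visit instead.** The SD of change is then 8.2 × √(2(1 - r)) and the ANCOVA SD is 8.2 × √(1 - r²). Power at r = 0.3, 0.5, 0.7 goes from 61.5%, 76.0%, 93.1% to 78.5%, 85.7%, 95.7%, again with the covariate charged.

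**6. Chance T0 imbalance.** With 8.2 as the SD of change, the T0 SD is 8.2 / √(2(1 - r)). At r = 0.5 that is 8.2, so the T0 arm difference has SE 2.73. An imbalance of one SE shifts the change contrast by (1 - 0.5) × 2.73 = 1.37 points, against a target of 7.5. As a share of the contrast variance this is 1.37² / 2.73² = 0.25, exactly 1 - 0.75. The imbalance shift and the loss of precision are therefore the same variance component.

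**7. Adding corrected age and centre.** With q = 3 the inflation is 33/30 = 1.10 on 31 df. If age and centre explain nothing beyond T0 IMP, power is 83%, 78%, 76% and 74% at r = 0.5, 0.7, 0.8 and 0.9. The gain over 76% has gone by r of about 0.8.

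**The case against.** The strongest reply is that the article never names a test. The IMP section defines the outcome variable, not the model, and an ANCOVA of change with T0 as covariate would fit it and give the same arm effect as an ANCOVA of T1. A full analysis plan might say so. This stands in part: it is a reason not to say that the article specifies an unadjusted test. But the article is not silent on baseline level. It places it, and places it at the second level.

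The second reply is that nothing here is invalid. That stands in full. A reader might infer that the T1 result is biased, or that chance imbalance is a further threat on top of the lost power. Under randomisation the change-score comparison is unbiased with its type I error intact, and the ordinary standard error already contains the imbalance component.

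The third reply is that r may be high: infants of different ages are retested after about four weeks, and the article reports an inter-observer ICC of 0.94 for the total score. The ICC is not r, but a high r is plausible, and there the gain is small.

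Two further inferences are not supported. One is that age must be adjusted for because entry is "corrected age at baseline: between 3 and 9 months"; the article gives no figure for how four-week IMP gain varies with age. The other is that baseline significance tests will decide what to adjust for. The Analyses section ties baseline differences to descriptive statistics and states no such rule.

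**Conclusion.** The point holds as one of efficiency, not validity. As the article assigns the analyses, the primary comparison is a T0-T1 change without T0 IMP as covariate. Adjusting for T0 IMP would raise power at 18 per arm by about 14, 10, 5 or 1 percentage points at r = 0.3, 0.5, 0.7 or 0.9. These figures rest on 8.2 being the SD of change, equal variances at the two visits, a two-sided test and independent infants. The article settles neither r nor the meaning of 8.2. The change is worth making because the data are already collected and, over this range of r, T0 IMP alone pays for its degree of freedom. The same cannot be said in advance of age and centre.

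**What to change.** Make the primary analysis a prespecified ANCOVA of T1 IMP (or, equivalently for the arm effect, of the change) on arm with T0 IMP as covariate. Report the adjusted difference with its 95% CI. Use the same form for AIMS and Teller Acuity Cards at T1, each with its own T0 value. Keep the effect-modifier model, with compliance and time of training, as exploratory. Say which SD 8.2 is.

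Corrected age at T0 may be added if it is expected to predict T1 IMP beyond T0 IMP. Age and centre each cost a degree of freedom and, if uninformative, could together remove the gain at r of about 0.8 or more, so the choice should be made and recorded before the data are unblinded.

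The cost is a change of wording and one residual degree of freedom (34 to 33). No extra infant, visit or measurement is needed.

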### Secondary outcome measures

#### Alberta Infant Motor Scale (AIMS)

This standardized scale examines delayed and abnormal motor development in infants overtime and it is a tool for assessment from term until 18 months of age [36]. AIMS assesses infant movement in four positions: prone, supine, sitting and standing, requiring about 20-30 minutes of administration time. The scale is quick to administer with limited handling and focuses on achievement of motor milestones, quality of posture and movement outcomes [37].

AIMS has been shown to be sufficiently sensitive to differentiate the motor development of preterm infants from that of full term infants. This evaluation will be carried out at all four time-points (T0-T3).

### BSID-III-Cognitive subscale

This scale is sensitive in detecting differences between a normative sample and children at risk for delayed development, such as premature infants. It has normative value referenced assessments, with means of 100 and Standard Deviation (SD) of 15 points. Children whose scores are 2 SDs below the normative value in a domain are considered as having a significant delay in that aspect of development. Bayley III is appropriate for administration to children between the ages of 1 month and 42 months (although norms extend downward to age of 16 days). The Bayley III revision includes Cognitive, Language, Motor, Social-Emotional, and Adaptive Behaviour scales. Items on the cognitive subscale assess sensor-motor development, exploration, manipulation, object relatedness, concept formation, problem-solving and memory [38]. This evaluation will be carried out at T0 and at T3.

### Teller acuity cards®

Teller Acuity Cards II is a test used to evaluate visual acuity in infants and children. It is based on judgement of the infant attention to a series of cards showing stripes of different widths. This tool allows rapid assessment of resolution (grating) visual acuity in infants and young children, and other populations where verbal response to recognition (letter) visual acuity charts is difficult or impossible [39–41]. It evaluates development of visual acuity and it has been used in several studies for diagnostic purposes and to measure the results of early intervention [18, 42, 43]. This evaluation will be carried out at all four time points (T0-T3). Visual Acuity assessment will complemented by quantitative evaluation of visual fixation and visual following, by means of an eye-tracker (CareToy for Clinics).

### Questionnaires

#### Ages & stages questionnaire® third edition (ASQ-3)

It has been developed as a screening tool for developmental delay in infants in numerous paediatric populations with reported easy administration, short completion time, easy interpretation, sensitivity, measure of true positives, and specificity, measure of true negatives, varying, with most studies reporting higher accuracy in at risk populations [32, 44–46].

The questionnaire covers from 1 to 66 months of age. The parents answer 30 questions that assess 5 domains of development, including communication, gross motor, fine motor, problem-solving, and adaptive skills. This self-administered assessment can be completed in 10 to 20 minutes and scored in 1 to 5 minutes.

The questionnaire will be given to parents after enrolment in order to define the most appropriate starting time for each infant (see inclusion criteria), Moreover, it will be given to the parents during all assessments in order to explore infant development from the parental point of view.

#### Social-emotional scale of BSID-III

It is a screening tool to measure social-emotional milestones in young children aged 0-42 months for early identification of social-emotional deficits and planning of the most successful interventions. It is filled out by the parents and contains 35 items, rated using a 5-point scale and ordered developmentally, according to age at which each item is typically mastered [47]. This questionnaire will be carried out at all time points (T0-T3).

#### Parenting Stress Index (PSI)

It is a self-report questionnaire designed to identify specific parental, child and situational characteristics most commonly associated with dysfunctional parenting [48]. Currently, the PSI is mostly used as a screening instrument for the early identification of parent-child systems, which are under stress and at risk of developing dysfunctional parenting behaviour. The validity of the PSI has been established in numerous studies on children with developmental problems, behaviour problems, disabilities and illnesses, as well as studies of at risk families and cross-cultural studies [49]. The questionnaire will be carried out at all time points (T0-T3).

### Analyses

Clinical Data will be managed and analysed using the Statistical Package for Social Sciences (SPSS). Descriptive statistics (means, standard deviation) will be calculated to summarise the data set for both groups and to identify potential baseline differences between the groups; p values will be used to indicate the strength of the evidence, and the Bonferroni correction for multiple assessments will be performed. The primary level of analysis will be the assessment of the effects of CareToy training at the primary endpoint (T1) in the primary and then in the secondary outcome measures. In the second level analysis we will provide multivariate statistics in order to take into account effect modifiers such as basal level of motor development, family compliance and time of training.

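### The sample size assumes the single primary test is made at an unadjusted 0.05, but the Analyses section states a Bonferroni correction whose scope is not limited and which does not exempt that test

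*Protocol article*

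**What the plan says.** - **Primary outcome** (Infant Motor Profile section): IMP is measured at all four time points, but "only the change from T0 to T1 will be used as the primary outcome". That is one outcome over one interval.
- **Sample size** section: the target is a "clinically relevant change of 7.5 points in the total IMP score", with SD 8.2, "at significance level of 0.05 and 80% power". The result is "A sample of 36 infants is required", and then "Considering a 10% of possible drop-outs a minimum of 40 infants will be recruited". No adjustment for multiplicity enters the calculation.
- **Analyses** section: the sentence that covers descriptive statistics, baseline differences and p-values ends with "the Bonferroni correction for multiple assessments will be performed". The next sentence puts the effect at T1 on the primary outcome first and the secondary outcomes after it. It attaches no significance level to that order and does not make the secondary tests conditional on the primary.
- **Outcome measures** section: three secondary outcomes are named, AIMS, BSID-III Cognitive and Teller Acuity Cards. The Abstract has all measurements taken at T0 and T1, whereas the BSID-III section schedules the Cognitive subscale at T0 and T3 only.

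**The concern.** A single pre-specified primary test needs no multiplicity correction, and the sample size was calculated on that basis. The Analyses section nevertheless states a named correction with no limits. Multiple assessments could mean several outcomes, several time points or several baseline comparisons. Under the first two readings the primary test could fall inside the family and be made at 0.05 divided by the number of tests.

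Two things are at stake. If the correction reaches the primary test, the trial has well under its stated 80% power for its own target difference. If the scope is left open until results are known, a primary p-value below 0.05 but above the corrected threshold could be called positive or negative on the same text.

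**Working it through.** **Inputs, all from the protocol article.** Difference 7.5, SD 8.2, level 0.05, power 80%, 36 evaluable infants and 10% drop-out come from the Sample size section. Equal groups come from the Randomisation section ("computer generated set of random pair 1:1 allocation"), so 18 per group. The article does not state sidedness. Two-sided is assumed, because the one-sided normal formula gives 15 per group, 30 in total, which is far from 36.

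**Step 1: the plan's own figure.** Normal formula for two means:

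n per group = 2 × [8.2 × (1.960 + 0.842) / 7.5]² = 18.76

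Rounded up, this is 19 per group, 38 in total; rounded down, it is 18 per group, the stated 36. The noncentral t gives 20 per group, 40 in total. The drop-out step reproduces exactly: 36 / 0.90 = 40. The stated size is therefore an unadjusted 0.05 calculation to within two infants.

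**Step 2: power at 18 per group with no correction.** The standard error of the difference is 8.2 × √(2/18) = 2.733, and 7.5 / 2.733 = 2.744. Normal power is Φ(2.744 − 1.960) = 78.3%. The noncentral t with 34 degrees of freedom gives 76.0%. The fair starting point is thus 76–78%, not 80%.

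**Step 3: power if the primary is inside a Bonferroni family of m tests.** Normal power is Φ(2.744 − z), with z the two-sided critical value at 0.05/m. For m = 4, z = 2.498 and Φ(0.246) = 59.7%.

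| m | Level | Power, normal | Power, t | Evaluable infants for 80% (normal / t) |
|---|---|---|---|---|
| 1 (primary exempt) | 0.05 | 78.3% | 76.0% | 38 / 40 |
| 2 | 0.025 | 69.2% | 65.6% | 46 / 50 |
| 3 | 0.0167 | 63.7% | 59.3% | 52 / 54 |
| 4 | 0.0125 | 59.7% | 54.8% | 54 / 58 |

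The value of m is an assumption. The primary plus three secondary outcomes gives 4. Leaving out BSID-III Cognitive, which its own section does not schedule at T1, gives 3. The three post-baseline IMP assessments (T1, T2, T3) also give 3.

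**Step 4: sensitivity to drop-out.** If all 40 recruited infants are analysed (20 per group), power is 80.5% (t) to 82.4% (normal) without correction and 60.9% to 65.3% at m = 4. The loss remains.

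**Step 5: how often the scope would decide the result.** If the true difference is 7.5, the chance that the primary p-value lies between 0.0125 and 0.05 is the difference between the m = 1 and m = 4 rows: 78.3 − 59.7 = 18.6 points (normal) or 76.0 − 54.8 = 21.2 points (t). That is about one trial in five.

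**The case against.** The strongest reply is that the article can be read consistently. It names one primary outcome, sizes the trial on it at 0.05, and analyses it before the secondary outcomes. The Bonferroni clause sits in the sentence about descriptive statistics and baseline differences, so it may concern only those comparisons or the other assessments. Nothing expressly puts the primary into the family. The article also condenses a fuller protocol, and the make-up of a multiplicity family is commonly settled in an analysis plan. Lastly, correcting the primary would be conservative: it costs power but does not inflate the type I error.

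Much of this stands. A reader might infer that power under the plan as written is about 55%. The documents do not support that. The figure requires the primary to be in the family, a family of exactly four, a t-test and exactly 36 evaluable infants, and the article fixes neither of the first two. A reader might also measure the loss from 80%, but a few points of that gap exist before any correction.

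What does not stand is that the point is only missing detail. The article did not leave multiplicity to another document. It states a correction without limits beside a sample size calculated with none. The order of analysis does not resolve this, because no significance level or gate goes with it. The consistent reading depends on an exemption that the reader has to supply.

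**Conclusion.** The concern holds in conditional form. The Sample size and Analyses sections agree only if the IMP T0 to T1 test is exempt from the Bonferroni correction, and the article does not say that it is. If the test is not exempt, power at 36 evaluable infants falls from 76–78% to 66–69%, 59–64% or 55–60% for families of two, three or four tests. Any family of two or more that includes the primary leaves power below 70%.

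These figures rest on the article's difference and SD, a two-sided test, equal groups of 18 and an assumed family size. They show what the open wording could cost and do not establish what power the trial has. If the primary is in fact tested at 0.05, the correction costs it nothing.

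**What to change.** In the Analyses section, state that the IMP change from T0 to T1 is the single confirmatory test, made at two-sided 0.05 without correction. State that the multiplicity correction applies only within the secondary outcomes at T1, tested after the primary, and use Holm in place of Bonferroni there. Holm gives the same family-wise protection and is never less powerful. List the outcomes in that family, which means settling whether BSID-III Cognitive is assessed at T1.

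The cost is one sentence of analysis wording and no additional infants, and the result matches the basis of the Sample size section. By contrast, keeping the primary in a family of four at 80% power would need 54 (normal) to 58 (t) evaluable infants, or 54 / 0.90 = 60 to 58 / 0.90 = 64.4, rounded up to 65, recruited. The small downside of the proposed wording is that confirmatory claims on secondary outcomes then depend on the primary result.
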